## Abstract

**Background:**

A high percentage of cervical cancer cases have not undergone cytological tests within 10 years prior to diagnosis. Different population interventions could improve coverage in the public system, although costs will also increase. The aim of this study was to compare the effectiveness and the costs of three types of population interventions to increase the number of female participants in the screening programmes for cancer of the cervix carried out by Primary Care in four basic health care areas.

**Methods/Design:**

A cost-effectiveness analysis will be performed from the perspective of public health system including women from 30 to 70 years of age (n = 20,994) with incorrect screening criteria from four basic health care areas in the Valles Occidental, Barcelona, Spain. The patients will be randomly distributed into the control group and the three intervention groups (IG1: invitation letter to participate in the screening; IG2: invitation letter and informative leaflet; IG3: invitation letter, informative leaflet and a phone call reminder) and followed for three years. Clinical effectiveness will be measured by the number of HPV, epithelial lesions and cancer of cervix cases detected. The number of deaths avoided will be secondary measures of effectiveness. The temporal horizon of the analysis will be the life expectancy of the female population in the study. Costs and effectiveness will be discounted at 3%. In addition, univariate and multivariate sensitivity analysis will be carried out.

**Discussion:**

IG3 is expected to be more cost-effective intervention than IG1 and IG2, with greater detection of HPV infections, epithelial lesions and cancer than other strategies, albeit at a greater cost.

**Trial Registration:**

**Clinical Trials.gov Identifier **NCT01373723

## Background

Cancer of the cervix is the second most frequent cancer in the world among women, with at least 400,000 new cases being detected every year [1]. Despite being one of the neoplasms with an easy preventive and therapeutic approach, it remains an important cause of morbid-mortality, although the figures in developed countries are lower than those in developing countries. In Spain, the incidence of cervical cancer is 7.1%, with a mortality of 3.1 cases per 100,000 women/year and showing a progressive trend [2]. In the Department of Pathologic Anatomy of our reference hospital C. H. Parc Taulí, 18 cases of invasive cervical cancer and 464 pre-malignant lesions (ASCUS, AGUS, LSIL, HSIL) have been diagnosed corresponding to women referred to our sexual and reproductive primary health care services (SRHC) from 2003 to 2008.

The aetiological cause of cervical cancer is infection by the human papilloma virus (HPV) [3]. Seroptypes 16 and 18 are the most prevalent types in our setting and, together with serotypes 45, 31, 33, 52, 58 and 35, are responsible for 90% of cervical cancer, with a global prevalence of 99.7% of cases[4,5]. The systematic vaccination of 12-year-old girls initiated in 2008 may have an important impact on the prevalence of HPV within 15 to 20 years, with a potential reduction of 67 to 71% of this virus [6]. High and continuous coverage of this vaccine in girls from 11 to 14 years of age may lead to a redefinition of screening, a variation in the schedules and, perhaps, the incorporation of primary screening with the HPV detection test in vaccinated women [7].

The Papanicolau cytology test introduced in the 1960s has allowed a reduction of up to 80% in the mortality by this disease with early diagnosis of precancerous lesions [8]. Thus, this continues to be the main diagnostic test used in screening programmes worldwide. One of the characteristics of the cytology test is its low sensitivity requiring periodical repetition. The test for the determination of HPV has recently been included in the screening programmes and, since 2006, 213 HPV positive cases have been detected in the study area.

In Catalonia, the protocol, which was revised and modified by the Oncology Management Director Plan and the Catalan Institute of Oncology in 2006, did incorporat the establishment of triennial periodicity of cytologies in women from 25 to 65 years of age as well as the incorporation of the HPV test in women from 40 to 65 years of age with no prior cytology within the previous 5 years or with a cytology carried out for longer than 5 years, abnormal cytology (no specified atypical squamous lesions) and women with post-conization control of intraepithelial lesions. The protocol also emphasizes the preventive role of the Basic Health Care Area (BHCA) and incorporates the figure of the midwife as a skilled professional for sample obtainment [9].

The research team decided to establish the age range for the population study between 30 to 70 years. The justification for the lower age limit is based on: 1.- although the second decade of life is when the greatest peak of infection by HPV is produced, the probability of its persistence is lower in young women, since the infection disappears in 90% of the cases after two years of follow up [7,10] 2.- early actions increase unnecessary interventions, generating anxiety in the woman and a work and economic overload on the public health care system [11]. 3.- establishing a limit after 30 years of age will detect the lesions derived from the persistence of HPV which, with treatment, will preserve fertility and avoid the evolution of the lesion towards invasive cancer [12].

In addition, the justification of the upper age limit is based on: 1.- recommendations of the Spanish Consensus for secondary prevention of cancer of the cervix in 2006 [13]. 2.- resolution num. 287 of the European Council (June 10, 2008 Luxemburg), related to the volume of cancer cases in the European Union and the mechanisms to reduce them [14]. 3.- an increase observed in the incidence of cancer in women born in the decade from 1930 to 1940 [2,13,14].

Eighty percent of the cases of cervical cancer in Catalonia have not undergone previous cytology during the 10 years prior to diagnosis [15]. Thus, an increase in screening coverage should be a priority objective for health care authorities if cervical cancer cases are to be reduced and women who do not periodically undergo cytology are to be identified. Some authors have reported that factors such as ethnic origin, age, education, and the socioeconomic levels condition participation in screening programmes [16]. Reasons to justify why women do not attend screening could include: (a) the perception of vulnerability; (b) the benefits perceived of screening; (c) anxiety; (d) bothersome; (e) fear of cancer; ans, (f) familial difficulties or personal circumstances [16,17]. With regard to the factors related to the health care system which influence the participation in screening in our setting, some authors have suggested: the absence of populational programmes, low sensitization with respect to preventive attitudes in cohorts of women of advanced age and the therapeutic health care overload in the primary care centres (PCC) [15].

The opportunistic preventive screening program in the Catalonian public health care system is carried out by the Sexual and Reproductive Health Care (SRHC) service located in the PCC and BHCA. The coverage of women attending our health care system (CIH) in 2008 (41.6%, figure obtained from the Systems of Primary Health Care Information (SPHCI) of the study setting) was similar to the one remaining at the SRHC of Catalonia.

A systematic review of the Cochrane collaboration [16], which evaluates interventions to stimulate the participation of women in the screening of this disease, concluded that invitations and educational interventions seem to be the most effective methods to increase absolute participation in the screening, although, to date, this has not been analysed from the point of view of efficiency.

At present, no study has evaluated from the efficiency point of view these interventions, though economic evaluation has been highly recommended for the cervical cancer screening programmes and HPV infections [18-20]. One key question influencing participation in screening programmes has been precision of population registers if an invitation letter is used (i.e. in some studies from 20 to 30% of the invited women were lost due to incorrect contact information) [21].

Due to the high prevalence of cervical cancer cases in this particular county we propose to launch a comparison of three different alternatives to improve the present coverage of the populational screening programmes in all the BHCA, therefore facilitating accessibility of population to the public health care system. The screening model proposed is centred on the recruitment of women with incorrect screening, performing cytology and the hybrid capture test for HPV to add diagnostic resolution due to the greater sensitivity of the test and the absence of screening in this population of women. Hence, systematic screening should be incorporated since these women have a greater risk of having cervical disease because of not having visited the health care system before. Therefore, this would facilitate earlier action in detecting pre-malignant lesions, helpingto t reduce the incidence of invasive cancer. To achieve so, the research team propose three different interventions, consisting in sending: (a) an invitation letter to participate in the screening; (b) an invitation letter and an informative leaflet; and, (c) an invitation letter, an informative leaflet and a phone call reminder. Therefore, there is: one common action in the three different interventions, which has been scientifically validated as effective, consisting in a personalized invitation letter sent by the primary health care professionals including a fixed appointment to undergo through a cytology test and, other two different interventions (informative leaflet and reminder call) to evaluate approaches for which there are few studies assessing the effectiveness of attendance to screening programmes. Following the indications of the National Health Care System to optimise the interventions of cancer prevention [18], the aim is to assess which is the most cost-effective intervention for a cervical cancer screening programme.

## Method/Design

An economic evaluation of three populational screening strategies for cervical cancer will be performed. (Figure 1, 2) Particularly, a cost-effectiveness analysis will be conducted. These interventions will be compared to the current opportunistic screening strategy using data of the multicentre randomised trial (CRICERVA). The analysis will be conducted from the National Health Care System perspective [22].

**Figure 1 F1:**
[figure not shown]
**Timing of the Project**.

**Figure 2 F2:**
[figure not shown]
**Study Algorithm**.

### Design

Pragmatic, blinded, multicentre, randomised, controlled clinical trial with four branches, and a three years follow-up. The randomisation unit was BHCA.

### Setting

Primary Health Care Services (PCS) of Cerdanyola-Ripollet, province of Barcelona, comprising 4 municipalities and 5 BHCA. The population covered by this PCS is 120,293 inhabitants over 14 years. As there are four study groups and 5 BHCAs, only 4 BHCAs with most homogeneous socioeconomic criteria will be considered.

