### Sample size

The sample size has been calculated based on the detection of a difference in effectiveness compared with the non intervention group (NIG). It has been calculated by multiplying the size of a simple randomised design by the design effect or factor of inflation. For the simple randomised design, on accepting an alpha risk of 0.05 and a beta risk of 0.20 in a bilateral contrast, 59 subjects will be required in the first group and 59 in the second group to detect a difference greater than or equal to 28.4% in the screening coverage of the 41.6% in the NIG. The lost to follow up rate has been estimated at 20%. The calculation of the sample has been performed with the Granmo 5.2 computer programme for Windows. According to a review of the literature [23-25], considering an intraclass correlation coefficient of 0.05 and a mean number of 3,500 women from 30 to 70 years of age with incorrect screening by BHCA, the design effect will be 176 and thus, 20,768 women with incorrect screening will be required.

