#### - Statistical analysis

All the statistical analyses will be performed using the SPSS v.18 programme and Microsoft Excel. The economic evaluation will be carried out according to the principle to be determined. Descriptive analysis of each of the groups will be performed. The mean values and standard deviations of the costs and the corresponding intervals of confidence at 95% will be presented. The final result will be reported in terms of effectiveness, cost and ICERs for each of the alternatives compared.

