## Limitations

Randomisation by groups will avoid the potential introduction of selection bias which may be produced among the interventions performed at the same site. Since the characteristics of the study do not allow the application of the double-blind masking technique, the masked response evaluation will be used to ensure that the measurement and interpretation of the dependent variables is carried out the same way in all groups. The possible loss of information, which may be produced in women doing screening outside public health care if they are not contacted by the research team, will be minimised with a phone call reminder. This will be made when the women do not attend the appointment. The language difficulties in women from other countries will be solved with cultural mediators at each site. Within the setting of the study, the administrative personnel have been updating the postal addresses of the users attending the BHCA since 2007 and, therefore the postal registry is quite precise, thereby reducing the potential loss of letters.

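### With one health care area per arm, intervention and area cannot be separated in the trial's own data, and the 80% power in the sample size section is not delivered

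*Protocol article*

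**What the plan says.** Four places in the protocol article bear on the unit of allocation.

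- **Design:** the trial is a "randomised, controlled clinical trial with four branches, and a three years follow-up", and "The randomisation unit was BHCA".
- **Setting:** "As there are four study groups and 5 BHCAs, only 4 BHCAs with most homogeneous socioeconomic criteria will be considered".
- **Limitations:** "Randomisation by groups will avoid the potential introduction of selection bias which may be produced among the interventions performed at the same site".
- **Abstract, Methods/Design:** "The patients will be randomly distributed into the control group and the three intervention groups".

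The first three describe allocation by area; the abstract describes allocation of women. The Sample size section sides with area allocation, because it multiplies an individual-level calculation by a design effect of 176 (ICC 0.05, mean of 3,500 women per area). It is set up "on accepting an alpha risk of 0.05 and a beta risk of 0.20 in a bilateral contrast" for one comparison with the non-intervention group, and gives no number of areas per arm.

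On inference, the Statistical analysis section says "The mean values and standard deviations of the costs and the corresponding intervals of confidence at 95% will be presented", without saying how the intervals are formed. The Uncertainty section plans a deterministic sensitivity analysis of parameters that it does not name.

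**The concern.** Four areas in four arms mean no replication within an arm. A difference in uptake, detection or cost between, say, the letter arm and the control arm is also the difference between two particular districts. Nothing in the trial data can apportion it.

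The plan acknowledges between-area variation by assuming an ICC of 0.05, but the design-effect approach works only if enough areas are replicated within each arm. Adding women to a single area does not help. The consequence runs downstream: the efficacy estimates from this trial feed the Markov model and the incremental cost-effectiveness ratios (ICERs), so a district difference could be reported as an intervention effect and then as a cost-effectiveness ranking.

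**Working it through.** **Inputs (protocol article).** Sample size: control coverage 41.6%; difference 28.4 points, so 70.0% under intervention; two-sided alpha 0.05; beta 0.20; loss 20%; ICC 0.05; 3,500 women per area. Population: 20,994 women. Design and Setting: four arms, four areas. My assumption: the 20,994 split equally, 20,994/4 = about 5,249 per area.

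**1. The plan's own figures reproduce.**
- Mean proportion = (0.416 + 0.700)/2 = 0.558.
- n = [1.96 x sqrt(2 x 0.558 x 0.442) + 0.842 x sqrt(0.416 x 0.584 + 0.70 x 0.30)]^2 / 0.284^2 = 46.8, so 47 per group.
- With losses: 47/0.80 = 58.75, so 59.
- Design effect: 1 + (3,500 - 1) x 0.05 = 175.95, so 176.
- Total: 2 x 59 x 176 = 20,768.

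**2. What that total implies.** Each of two groups needs 59 x 176 = 10,384 women, and 10,384/3,500 = 2.97, about three areas per arm. The design has one.

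**3. Degrees of freedom.** Four areas minus four arm means leaves 0. For a pairwise contrast with k areas per arm it is 2(k - 1) = 0 at k = 1.

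**4. Power if ICC 0.05 is taken as known.** Effective n per arm = m/[1 + (m - 1) x 0.05].
- m = 3,500: 3,500/175.95 = 19.9.
- m = 5,249: 5,249/263.4 = 19.9.
- The ceiling is 1/0.05 = 20, however many women are included.

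Power at n = 19.9, by the formula in step 1: the normal deviate is (0.284 x sqrt(19.9) - 1.96 x 0.702)/0.673 = -0.16, giving about 44%. With an unpooled standard error it is about 47%.

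For comparison, a cluster-level t-test at ICC 0.05 (standard error of a one-versus-one difference about 15.1 points, divided by sqrt(k)) has power of about 33% with two areas per arm, 69% with three and 88% with four.

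**5. How far two untreated areas could differ.** Between-area SD of a difference = sqrt(2 x ICC x 0.416 x 0.584); the 95% range is 1.96 times that. Type I error of a test by woman that ignores area = 2 x [1 - Phi(1.96/sqrt(DE))], with DE = 1 + (5,249 - 1) x ICC.

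| ICC | 95% range, two untreated areas | DE | Type I error if area is ignored |
|---|---|---|---|
| 0.001 | +/-4.3 points | 6.2 | 43% |
| 0.01 | +/-13.7 points | 53.5 | 79% |
| 0.05 | +/-30.5 points | 263.4 | 90% |

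At the plan's ICC, the range exceeds the 28.4-point target difference. It does so for any ICC above about (0.284/1.96)^2/(2 x 0.243) = 0.043.

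**The case against.** **One area per arm is inferred.** The article does not say so outright, and the study algorithm figure is not shown. But keeping four of five areas because there are four groups, with the area as randomisation unit, leaves no other natural reading. The abstract alone points elsewhere.

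**Areas were chosen for socioeconomic similarity.** This may lower the true ICC, and 0.05 is a planning value from literature. Also, 41.6% is the 2008 coverage of women attending the health system, which need not equal uptake among women already overdue. At an assumed 10% uptake and ICC 0.05 the between-area SD would be sqrt(0.05 x 0.10 x 0.90) = 6.7 points rather than 11.0. This stands, and is why a range of ICCs is shown. The type I error column does not depend on the uptake level, and it is still 43% at ICC 0.001. Similarity is not replication.

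**The article specifies no analysis of uptake that ignores area.** Correct. A reader might infer from the planned 95% intervals that the trial commits to such an analysis. The text does not support that: the intervals concern costs, their method is not given, and a condensed article may leave it to another document. The error rates above are conditional on area being ignored.

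**Group allocation has a real benefit.** A reader might take the Limitations section to claim that it removes selection bias generally. The sentence is restricted to interventions running at the same site, which is close to a statement about contamination. Its wording is loose, and it is silent on differences between areas.

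**Conclusion.** The concern holds in this form: with one area per arm, intervention and area are fully confounded, the trial's own data cannot estimate between-area variance, and the stated 80% power is not achieved. At the plan's ICC of 0.05, power is about 44% (effective n about 20 per arm against 47), even with the ICC treated as known. No analysis plan can recover the missing replication, so this is not a detail left to another document. Separately, the abstract contradicts the Design section on the unit of allocation.

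Two stronger readings are not supported. First, a reader might conclude that no valid interval can exist at all. One can be built, but only with an imported ICC or an assumption such as equal area trends, which these data cannot test. Second, a reader might call the study non-randomised. The Design section says that areas were randomised; the defect is lack of replication.

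The sizes rest on an equal split of 20,994 women, roughly normal area effects and, for the ranges in points, the 41.6% control figure.

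**What to change.** **If allocation is not yet implemented:** randomise women, or GP-nurse teams (UBAs), to the four arms within each BHCA, stratified by BHCA. Letters, leaflets and calls go to individual women, so mailing lists can be split. If UBAs are used, clustering at that level still has to enter the sample size; the article does not give their number. The cost is an amendment, all materials being handled at every site, and some contamination between neighbours. The Design section uses the past tense, so this may be too late.

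**If allocation is fixed:**
1. Describe the study as an unreplicated cluster allocation, one area per arm, and correct the abstract's statement on how patients are distributed.
2. Restate the power in Sample size for one cluster per arm.
3. Report intervals for effects, costs and ICERs that include a between-area variance, over a range of assumed ICCs that includes 0.05, and vary the effect over the same range in the sensitivity analysis.
4. As a separate sensitivity analysis, give a difference-in-differences estimate if historical BHCA-level uptake for a comparably defined cohort can be extracted from the primary care information system. State its equal-trends assumption. Do not apply the cross-sectional ICC to it, because differencing removes stable area differences and leaves area-by-time variation, a different quantity.
5. Reword Limitations to say that group allocation limits contamination between interventions at the same site and does not remove differences between areas.

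Items 1, 2 and 5 are wording and one recalculation. Item 3 costs wider intervals. Item 4 needs a data extract whose availability the article does not establish.

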### Population

20,994 women from 30 to 70 years of age with incorrect screening criteria (data obtained from SPHCI) ascribed to the BHCA will be included in the study. Incorrect screening will be defined as [9]: 1.- No cytology in the last 3 years from women between 30 to 40 years, 2.- No cytology in the previous 5 years from women between 40 to 65 years, 3.- No previous cytology history for females older than 65 years or women who have not had their last cytology before the age of 60. The exclusion criteria will be: (a) hysterectomised women, with a current history of pre-malignant lesions (AGUS, ASCUS, LSIL, HSIL), carcinoma in situ and cervical-uterine cancer, HIV positive or other causes of immunosuppression (since these women follow a specific protocol); (b) those residing outside the study setting for more than 6 months; and (c) those ascribed to the study BHCA but with a physician assigned in an UBA of another zone different from the one considered in the study.

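### The second branch of the over-65 criterion for incorrect screening is worded in reverse of the other criteria and of the trial's stated target

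*Protocol article*

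**What the plan says.** The Population section gives the cohort as "20,994 women from 30 to 70 years of age with incorrect screening criteria", taken from the primary care information system (SPHCI). It defines incorrect screening, citing the regional protocol, by three criteria:

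- Criterion 1: "No cytology in the last 3 years from women between 30 to 40 years".
- Criterion 2: "No cytology in the previous 5 years from women between 40 to 65 years".
- Criterion 3, first branch: "No previous cytology history for females older than 65 years".
- Criterion 3, second branch: "women who have not had their last cytology before the age of 60".

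The Background states the purpose: "The screening model proposed is centred on the recruitment of women with incorrect screening". It gives as the reason that "these women have a greater risk of having cervical disease because of not having visited the health care system before".

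**The concern.** Criteria 1 and 2 and the first branch of criterion 3 all point the same way: the absence of a test, or of a recent one, makes a woman eligible. The second branch of criterion 3 points the other way. If a woman's last cytology was not before 60, it was at 60 or later, so the branch admits those tested later in life and leaves out those whose last test is furthest in the past.

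This matters because the eligible list comes from a database, and a query applies the rule it is given. If the sentence was followed as printed, the over-65 part of the cohort would include recently tested women and lack some of the long-overdue women the trial is meant to reach. If a different rule was run, the published definition does not describe the cohort and the count of 20,994 cannot be reproduced from it. The sentence needs correcting in either case.

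**Working it through.** **Step 1: the plan's own figure.** The Sample size section sets "an alpha risk of 0.05 and a beta risk of 0.20 in a bilateral contrast", coverage of 41.6% without intervention, a difference of 28.4 points, 20% loss, an intraclass correlation of 0.05 and 3,500 women per area.

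- Proportions: 0.416 and 0.416 + 0.284 = 0.700; their mean is 0.558.
- Per group: n = [1.960 × √(2 × 0.558 × 0.442) + 0.842 × √(0.416 × 0.584 + 0.700 × 0.300)]² / 0.284² = 46.8, rounded up to 47.
- With 20% loss: 47 / 0.80 = 58.75, rounded up to 59, as stated.
- Design effect: 1 + (3,500 − 1) × 0.05 = 175.95, rounded to 176, as stated.
- Total: 2 × 59 × 176 = 20,768, as stated.

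The figure reproduces. Criterion 3 enters none of these steps, so the wording problem does not alter it.

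**Step 2: apply criterion 3 to individual cases.** The second branch does not repeat the age limit; I take it to be governed by the over-65 limit of the first branch. Three rules are compared:

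- As worded: eligible if never tested, or if age at last test is 60 or more.
- Negation removed: eligible if never tested, or if age at last test is below 60.
- Recency rule: eligible if there has been no test in 5 years. This carries criterion 2's window past 65 and is an assumption for illustration only.

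| Age | Age at last test | Years since | As worded | Negation removed | No test in 5 years |
|---|---|---|---|---|---|
| 66 | never | – | yes | yes | yes |
| 66 | 65 | 1 | yes | no | no |
| 66 | 59 | 7 | no | yes | yes |
| 66 | 60 | 6 | yes | no | yes |
| 68 | 55 | 13 | no | yes | yes |
| 70 | 69 | 1 | yes | no | no |
| 70 | 40 | 30 | no | yes | yes |
| 70 | 62 | 8 | yes | no | yes |

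**Step 3: read the table.**

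- Women tested one year ago qualify as worded and under neither alternative.
- Women last tested before 60 (7 to 30 years ago in these cases) fail as worded and qualify under both alternatives.
- Never-screened women qualify throughout.
- Women of 66 last tested at 60, or of 70 last tested at 62, qualify as worded and under the recency rule, but not if the negation is simply deleted. The two obvious repairs therefore disagree, and the article alone does not settle which was intended.

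**The case against.** The best defence is that this is a language slip. The article has other visible ones, the definition is attributed to a cited regional protocol, and the Background makes the intended population plain. Nothing shows that the SPHCI query followed this English sentence. The same definition is stated for every arm, so the wording implies no differential selection between arms. Most of this stands: a slip is the likely cause, and damage to the actual cohort is possible but not shown. It does not rescue the sentence, which is a stated eligibility rule that would give the wrong list if followed and is not corrected anywhere else.

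A reader might infer more than the article supports, in three ways:

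- That every previously tested woman over 65 is classified the wrong way round. That holds only against the version with the negation deleted. Against a recency rule, a woman of 70 last tested at 62 is eligible either way.
- That the number misclassified can be estimated by applying an assumed age share for 66 to 70 to the 20,994. That would give the size of an age band, not an error count. It would include never-screened women, who are unaffected. If the literal rule had been run, it would miss the overdue women who had been left out. The article gives no age distribution.
- That the shared boundary at 40 in criteria 1 and 2 is a second defect of substance. It is ordinary shorthand at a single age and carries no weight.

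**Conclusion.** The point holds as an internal contradiction in an eligibility rule. The second branch of criterion 3 runs against criteria 1 and 2 and against the target population in the Background. It concerns only previously screened women over 65, within a cohort that runs to 70. How many women that is, and how many would change status, cannot be computed from the article. The sample size of 20,768 is unaffected. The conclusion rests on the literal reading of the sentence and on taking the second branch as limited to women over 65. It does not establish that the 20,994 is wrong, because the article does not show which rule produced that count.

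**What to change.** Reword the second branch of criterion 3 so that it agrees with criteria 1 and 2 and with the cited regional protocol, taking the age cut-off from that source; none is proposed here. Check which rule the SPHCI extraction used and state it. If the intended rule was run, correcting the sentence is enough. Only if the literal rule was applied should the extraction be repeated and the 20,994 restated. The age bands meeting at 40 can be made non-overlapping in the same edit.

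The cost is one corrected sentence and a look at the stored query, plus a repeat query if the check requires it. If letters have already gone out, reporting the rule actually used still makes the denominator interpretable.
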